## Abstract

**Background:**

Literature regarding the advantages of gasless vNOTES is insufficient. The aim of our study is to compare gasless vNOTES vs. traditional vNOTES on hemodynamic profiles and outcomes in patients with benign gynecological disease. We hypothesize that compared with those in the traditional vNOTES group, hemodynamic profiles will be changed less during gasless vNOTES, while safety can be promised.

**Methods:**

This is a single-center, prospective, single-blind, randomized controlled clinical trial, which has been approved by the Institutional Review Board of Chengdu Women’s and Children’s Hospital on September 27, 2022. One hundred and twenty patients will be recruited and randomly assigned to either the traditional vNOTES group or the gasless vNOTES group in a 1:1 ratio. For patients allocated to the traditional vNOTES group, after insertion of one port through the vagina, CO_2_ gas is infused with a pressure of 12–14 mmHg; while for those allocated to the gasless vNOTES group, a special device is used as an abdominal wall-lifting device to facilitate gasless surgery. CO_2_ pneumoperitoneum will not be used during the whole gasless vNOTES procedure. The primary outcome is vital signs at different time points. The secondary outcomes include surgical conversion rate, duration of surgery and anesthesia, anesthetic consumption, intraoperative estimated blood loss, VAS and PONV scores at postoperative 2 h and 24 h, administration of vasopressor drugs from the beginning of general anesthesia induction to 15 min after endotracheal intubation, including times, dosage, and type, intraoperative and postoperative complications, time of first getting out of bed after surgery, and time of first eating after surgery, including light drink.

**Discussion:**

This is the first randomized controlled trial to compare the impacts of gasless vNOTES vs. traditional vNOTES on hemodynamic profiles and outcomes in patients with benign gynecological disease. If a favorable effect and safety of gasless vNOTES for hemodynamic profiles and outcomes in patients are shown, gasless vNOTES would be an optimal treatment option for patients with benign gynecological disease.

**Trial registration:**

The trial was registered at https://www.chictr.org.cn/showproj.html?proj=182441 with registration No. ChiCTR2200064779 on Oct 17, 2022.

**Supplementary Information:**

The online version contains supplementary material available at 10.1186/s12871-023-02322-7.

## Background

Since Transvaginal Natural Orifice Transluminal Endoscopic Surgery (vNOTES) was applied and reported in 2007 by Marescaux et al., this technique has been increasingly conducted in the field of gynecology, such as hysterectomy [1, 2], adnexectomy [3], and myomectomy [3, 4]. Published literature has proved that, compared to traditional laparoscopic surgery, vNOTES hysterectomy is associated with a lower pain score after surgery and a shorter length of hospital stay [1]. Due to its minimally invasive and without abdominal incisions, maximum aesthetics can be achieved.

During the routine vNOTES procedure, carbon dioxide (CO_2_) pneumoperitoneum is required. CO2 insufflation may induce hemodynamic instability and acid–base imbalance. A well-summarized review has reported that acidosis, inflammation, oxidative stress, and hypothermia may all be associated with CO_2_ pneumoperitoneum [5]. Moreover, in an animal study, the authors found that an inflammatory response was evoked during pneumoperitoneum [6]. Additionally, the transvaginal insertion of devices to establish CO_2_ pneumoperitoneum makes the already narrow surgical space even more crowded, further exacerbating the inconvenience of transvaginal operations [7]. In 2014, Chen et al. performed the first transvaginal appendectomy under gasless laparoscopy [7]. Subsequently, they reported that transvaginal salpingo-oophorectomy with gasless laparoscopy was successfully conducted in ten patients [8]. However, technical difficulties associated with gasless laparoscopy, such as limited abdominal space and poor surgical visualization restrict its application.

To date, literature regarding the advantages of gasless vNOTES is insufficient. Most studies related to gasless vNOTES are case series, which is not convincing enough. Thus, the aim of our study is to compare gasless vNOTES vs. traditional vNOTES on hemodynamic profiles and outcomes in patients with benign gynecological disease. The primary outcome is the changes in mean arterial pressure (MAP) and heart rate (HR) at different time points during the surgery. The secondary outcomes will be surgical conversion rate and complications. We hypothesize that compared with those in the traditional vNOTES group, hemodynamic profiles will be changed less during gasless vNOTES, while safety can be promised.

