### Sample size estimation

The sample size calculation was based on the changes in patients' blood pressure at the beginning of surgery. Since no similar studies have been conducted before, a pilot study was conducted previously. According to the results of the pilot study, in the traditional vNOTES group, 50% of patients had a greater than 20% change in blood pressure at the beginning of the CO_2_ pneumoperitoneum. Due to the different surgical strategies, CO_2_ pneumoperitoneum is not required in the gasless vNOTES group. We assume that the number of patients with a blood pressure change of more than 20% is less in the gasless vNOTES group than in the traditional vNOTES group. The 10% reduction in the gasless vNOTES group was considered to be statistically significant. A statistical power of 80% and a one-sided α significance level of 0.05 were used for power analysis with 1:1 allocation. A sample size of 49 patients in each arm was estimated. Considering a dropout rate of 20%, 60 patients for each group were enrolled.

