### Statistical methods

Data will be analyzed by using R studio 4.2.2 for Windows (Armonk, NY, United States). Data from the primary outcome will be presented as mean ± standard deviation if normally distributed, and t-test will be conducted; otherwise, the data will be reported as median (IQR), and no-parametric tests will be performed. Categorical data will be summarized as frequencies (percentages) and compared between study groups using χ2 tests or Fisher exact tests, as appropriate. *P* value < 0.05 was considered significant.

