## Discussion

This is the first randomized controlled trial to compare the impacts of gasless vNOTES vs. traditional vNOTES on hemodynamic profiles and outcomes in patients with benign gynecological disease. It is noted that pneumoperitoneum and carbon dioxide insufflations which are required during traditional vNOTES may lead to an increase in plasma catecholamine levels and plasma renin activity. Besides, the increased intra-abdominal pressure may lead to reduced thoracic and pulmonary compliance. All these changes result in an increase in heart rate, blood pressure, and reduced cardiac output. Moreover, a systematic review has well-summarized the “dark” disadvantages related to pneumoperitoneum effects, such as leading inflammatory response, inducing acidosis, producing reactive oxygen species, and adhesion development [5]. However, CO2 insufflation can provide a better visualization of the surgical field, which may shorten surgical duration and decrease surgical-related complications. If a favorable effect and safety of gasless vNOTES for hemodynamic profiles and outcomes in patients are shown, gasless vNOTES would be an optimal treatment option for patients with benign gynecological disease. Additionally, previous studies have proved that the use of vNOTES may be particularly effective and safe for selected populations, such as obese women, and women with large uteri [12, 13]. In our study, we may find that the application of gasless vNOTES is suitable for patients with abnormal cardiopulmonary functions.

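### Safety is part of the hypothesis and a condition of the main conclusion, but the only stated analysis is a difference test that cannot establish it at 60 per arm

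*Protocol article*

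**What the plan says.** The Background section of the protocol article gives a two-part hypothesis, repeated in the Abstract: "hemodynamic profiles will be changed less during gasless vNOTES, while safety can be promised". The Discussion turns the second part into a condition for the recommendation. It begins "If a favorable effect and safety of gasless vNOTES for hemodynamic profiles and outcomes in patients are shown" and concludes that "gasless vNOTES would be an optimal treatment option for patients with benign gynecological disease". The Abstract repeats this as well.

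The Background names surgical conversion and complications as the secondary outcomes; the Outcome measures section lists both among a longer set. The safety section defines the complications as bowel, ureter and bladder injury, surgical site infection within 14 days, and unplanned secondary surgery.

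The trial was not sized on any of these: "The sample size calculation was based on the changes in patients' blood pressure at the beginning of surgery". The result was 49 per arm, raised to 60 for dropout. Under Statistical methods, categorical data are to be "compared between study groups using χ2 tests or Fisher exact tests, as appropriate", with significance at P < 0.05. The document gives no safety margin, acceptable complication rate, expected complication rate or precision target.

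**The concern.** A difference test asks whether the data contradict equal risk. When it is significant, it shows harm or benefit. When it is not, it shows only that the data were insufficient to separate the arms, which says little when events are few. To claim safety, one must rule out an excess, or an absolute rate, that would be unacceptable. That requires either a margin or a confidence interval set against a stated limit.

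The protocol makes safety one of two conditions for its recommendation but specifies only the difference test. The question is not idle, because the document itself gives reasons to expect a possible excess. The Background mentions restricted space and poor visualisation with gasless laparoscopy, and the Discussion says that CO2 insufflation may reduce surgical complications. At stake is whether the final report can support a statement about the safety of a newer technique.

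**Working it through.** **Inputs from the protocol.** 60 enrolled and 49 evaluable per arm (Sample size estimation); χ2 or Fisher test, P < 0.05 (Statistical methods). The protocol states no figure for safety, so there is none to reproduce. The derivation of the 49 is a separate matter on which this point does not depend.

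**Assumption.** All complication rates in step 3 are assumed. Steps 1 and 2 need no assumed rate.

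**1. How large an imbalance is still non-significant?** With 0/60 in one arm and k/60 in the other, the two-sided Fisher P value is 2 × C(60,k) / C(120,k).

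- k = 5: 2 × 5,461,512 / 190,578,024 = 0.057
- k = 6: 2 × 50,063,860 / 3,652,745,460 = 0.027

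So five complications against none is not significant, and six against none is needed. With five events in total, the expected count is 2.5 per arm, so Fisher is the natural choice under the protocol's own provision for picking the appropriate test. A continuity-corrected χ2 gives P = 0.068. Only the uncorrected χ2, doubtful at such counts, falls below 0.05 (120 × 300² / (60 × 60 × 5 × 115) = 5.22, P = 0.022).

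**2. What does a perfect result exclude?** With zero events in n patients, the exact upper limit is 1 − 0.05^(1/n) for a one-sided 95% bound, and 1 − 0.025^(1/n) for the upper end of a two-sided 95% interval.

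| n | One-sided 95% | Two-sided 95% |
|---|---|---|
| 60 | 4.9% | 6.0% |
| 49 | 5.9% | 7.3% |

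For the difference between arms, zero events in both arms of 60 gives a Newcombe 95% interval of about ±6.0 percentage points. The Wilson upper limit is z²/(n + z²) = 3.84/63.84 = 6.0%, and the other arm contributes nothing to the width on that side.

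**3. Power to detect harm under assumed rates.** The exact power is the sum of Bin(a; n, p1) × Bin(b; n, p2) over all pairs (a, b) whose two-sided Fisher P is below 0.05.

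| Traditional vs gasless (assumed) | Power, 60 per arm | Power, 49 per arm |
|---|---|---|
| 1% vs 5% | 4.6% | 2.2% |
| 2% vs 6% | 5.5% | 3.0% |
| 2% vs 10% | 27.7% | 18.2% |
| 5% vs 15% | 32.6% | 23.5% |
| 10% vs 30% | 73.0% | 62.7% |

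A threefold to fivefold excess is usually missed when the control rate is 1% to 5%. A threefold excess on a control rate of 10% is usually found.

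**4. Would a margin have helped?** Assume equal true rates, one-sided α of 0.025 and 80% power, so that n per arm is about (1.960 + 0.842)² × 2p(1 − p) / margin². For a margin of 5 points, this gives 63 per arm at p = 1%, 124 at 2% and 299 at 5%. For a margin of 10 points, it gives 16, 31 and 75. So 60 per arm could support a formal safety claim only with a low event rate and a wide margin, and the protocol states neither.

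**The case against.** **No stated rule equates non-significance with safety.** A reader might infer that the plan will report a non-significant complication test as safety. The documents do not support this. Statistical methods says only how categories are compared, and the Discussion is conditional without saying what would count as demonstration. This objection stands. What remains is that the protocol requires a demonstration and offers no other means of making one.

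**Non-significance is not a foregone conclusion.** A reader might also infer that the test is almost certain to miss even a severalfold excess. That depends on rates the protocol does not give. At 2% vs 10% the chance of missing the difference is about 72%, and at 10% vs 30% it is about 27%. This too stands, and it limits the power argument to the rates assumed.

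**Safety is secondary and loosely worded.** Complications are secondary outcomes, no non-inferiority claim is made, and small surgical trials are seldom powered for rare harms. That is fair, and lack of power for rare events is no design error by itself. But the expectation appears in both Abstract and Background, and the recommendation depends on it.

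**Other safety provisions exist.** Conversion is defined as an outcome, including a change from gasless surgery to CO2, and the principal investigator can terminate the trial for severe events. These are real safeguards, but they supply no criterion for concluding that the technique is safe.

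**Intervals may be in a fuller document.** Interval methods are commonly left to an analysis plan, so their absence from the article is not the finding. The finding is a stated hypothesis and conclusion that the stated size and test cannot carry.

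**Conclusion.** The point holds as a mismatch between claim and method. Safety is hypothesised and is a condition of the recommendation, but the stated difference test in a trial sized on blood pressure cannot establish it. Without any assumed rate, five complications against none gives Fisher P = 0.057, and an event-free arm of 60 still leaves a rate of up to 4.9% (one-sided) or 6.0% (two-sided), or 5.9% and 7.3% with 49. The power figures, about 5% to 73% at 60 per arm, rest on assumed rates and illustrate a range. The primary haemodynamic analysis is unaffected. The correction should be made because it changes what the trial may legitimately conclude.

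**What to change.** Before the data are analysed:

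1. Restate the safety half of the hypothesis (Abstract and Background) as an aim to estimate complication and conversion rates in each arm.
2. Report each rate, and each between-arm risk difference, with an exact 95% confidence interval, for example Clopper–Pearson for single rates and an exact unconditional interval for differences.
3. State in Statistical methods that a non-significant χ2 or Fisher test on complications or conversion will not be taken as evidence of safety or equivalence.
4. Reword the conclusion in the Abstract and Discussion so that it rests on the haemodynamic result, with the upper confidence limit for complications quoted beside it.

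This takes a protocol amendment and a few added intervals, with no new patients or data. The price is a more modest claim: the trial could say how large a complication rate its data exclude, but not that safety has been shown. If the sponsor wants a formal safety claim, it needs a justified margin, an expected rate and a sample size based on both. Under the assumptions in step 4 of the working, that would often mean more than 60 per arm.

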## Methods/design

### Study design, ethics, and trial registration

This is a single-center, prospective, single-blind, randomized controlled clinical trial. This study was approved by the Institutional Review Board of Chengdu Women’s and Children’s Hospital on September 27, 2022 [IRB approved number: 2022(112)]. The study protocol has been structured in according with the SPIRIT 2013 Statement [9] and CONSORT 2010 guidelines [10]. The trial was registered at https://www.chictr.org.cn/showproj.html?proj=182441 with registration No. ChiCTR2200064779 on Oct 17, 2022. The written informed consent will be obtained from all patients before enrollment in the study.

### Patient inclusion and exclusion criteria

#### Inclusion criteria

Patients aged ≧18 years and ≦60 years;Body mass index (BMI) 18–25 kg/m^2^;Patients with benign gynecological disease, including adenomyosis of the uterus, uterine fibroids, ovarian cysts, tubal lesions, and other non-malignant gynecological diseases;Patients are scheduled to undergo vNOTES surgery, under general anesthesia;American Society of Anesthesiology (ASA) status I–III;Patients are willing to participate and provide signed written consents for the clinical study.

#### Exclusion criteria

The patients will be excluded if they meet the following criteria: (1) Patients without sexual activities before surgery; (2) The patient is pregnant or lactating; (3) The anticipated surgical duration is longer than 180 min, which will be judged by the surgeon; (4) Patients with a history of two or more cesarean sections, suspected rectovaginal endometriosis, suspected malignancy, or active lower genital tract infection; (5) Participating in other clinical studies within 3 months.

### Enrollment of participants and allocation

#### Consent to participate, enrollment of participants

Written informed consent by patients or their authorized surrogates will be required in this trial. Investigators who have been trained for the study procedures will screen potential candidates before surgery, according to the inclusion and exclusion criteria. The patients will be informed of the advantages, disadvantages, and potential risks of participating in the current study. The patients or their authorized clients should give written informed consent.

#### Allocation, Randomization, and blinding

This is a randomized, double-blind controlled clinical trial. One hundred and twenty patients will be recruited and randomly assigned to either the traditional vNOTES group or the gasless vNOTES group in a 1:1 ratio. A researcher from the anesthesiology department who is not involved in the current study will generate the randomized allocation number and distribute the allocated opaque envelope. The envelope will be delivered directly to the surgeon who is responsible for performing the surgery. The researchers involved in the postoperative assessment and the researchers analyzing the data are blinded to the groups’ assignment. When consent for trial participation is obtained from the participant, the physician will double-check the medical number, age, gender, and primary disease of the participant before unsealing the envelope to avoid reallocation and confirm their allocation. The study flow chart is presented in Fig. 1. The study process and evaluation are reported in Table 1. This study is in accordance with SPIRIT reporting guidelines, which are attached as an online Supplemental file 1.

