### Data collection

The following data will be collected during the study. To guarantee the study quality, all the investigators will be trained and pass the examinations. The trained investigator (YW) who will be blinded to the allocation will collect intraoperative data. KL, QH, and QZ will do the anesthesia procedures and collect intraoperative data, respectively; to avoid bias, they will not participate in postoperative data collection. All the statistical analyses will be performed by one of the corresponding authors (YC).Demographic data: Age, BMI, ASA status, clinical diagnosis, history of spontaneous delivery, abdominal surgery history, and surgical index.Intraoperative data: The MAP and HR prior to induction (T0), at the time point of intubation (T1), 10 min after tracheal intubation (T2), surgical incision immediately (T3), 10 min after surgical incision (T4), 10 min before the end of surgery (T5), at the end of surgery (T6), and at the time point of tracheal extubation (T7); duration of surgery; duration of anesthesia; the consumption of anesthetics (including sufentanil and cisatricurium); consumption of vasoactive drugs (including nitroglycerin and metaraminol); intraoperative estimated blood loss. Intraoperative complications include bowel, ureter, and bladder injury.Postoperative data*Postoperative pain assessment* All patients will be guided to use a 0 to 10 cm visual analogue Scale (VAS) to express the degree of pain. VAS scores are collected at the time of 2 h after surgery and 24 h after surgery. Additional analgesic medications are available at the patient’s request. Number of patients who have a requirement for rescue analgesia are recorded. Postoperative rescue analgesia can be provided by intravenous injection of 5 μg sufentanil or ketorolac 30 mg.*Postoperative adverse events *The incidence of postoperative nausea and vomiting (PONV) during postoperative 24 h are recorded. Nausea is referred to the patient with uncomfortable feeling in their stomach, and the severity of nausea is evaluated as follows*:* none = 0, mild = 1, moderate = 2*.* If there is gastric content vomited out, it is scored as 3. Rescue antiemetic could be offered to any patient who has a nausea score > 2. Postoperative complications include surgical site infection within 14 days, and unplanned secondary surgery related to this surgery.

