### Outcome measures

1. The primary outcome is vital signs at the different time points, including before anesthesia (baseline: T0), at endotracheal intubation (T1), 10 min after endotracheal intubation (T2), at the beginning of the operation (T3), 10 min after the operation (T4), 10 min before the end of the operation (T5), at the end of the operation (T6) and at the time of tracheal extubation (T7).2. The second outcomes are collected as follows.①Surgical conversion rate refers to the surgeon cannot complete the surgery in the scheduled mode of operation, and has to convert to open abdominal surgery or traditional multiport laparoscopic surgery, or single port laparoscopic surgery. For the patient who is allocated to the gasless vNOTES group, the surgeon requires the use of traditional vNOTES with CO_2_ pneumoperitoneum if they are unable to complete the surgery under gasless vNOTES, and this patient is considered as a surgical conversion. If the operation cannot be completed according to the scheduled surgical method, the surgical strategy can be changed as appropriate.② Duration of surgery (from speculum placement to suturing the wound)③ Duration of anesthesia (from anesthesia induction to endotracheal extubation)④ The anesthetic consumption during the surgery, including sufentanil and cisatracurium⑤ Intraoperative estimated blood loss⑥ VAS and PONV scores at postoperative 2 h and 24 h.⑦ Administration of vasopressor drugs from the beginning of general anesthesia induction to 15 min after endotracheal intubation, including times, dosage, and type.⑧ Intraoperative and postoperative complications (e.g., bowel, ureter, and bladder injury, surgical site infection, and unplanned secondary surgery).⑨ Time of first getting out of bed after surgery⑩ Time of first eating after surgery after surgery, including light drink.

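### The named t or nonparametric tests leave T0 MAP/HR and diagnosis unused in a mixed uterine and adnexal population: valid, but less precise than the collected data allow

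*Protocol article*

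**What the plan says.** - **Population** (Inclusion criteria): benign disease "including adenomyosis of the uterus, uterine fibroids, ovarian cysts, tubal lesions, and other non-malignant gynecological diseases". The Background names hysterectomy, adnexectomy and myomectomy among the uses of vNOTES, and Surgical technique says that the tissue removed depends on where the lesion lies.
- **Allocation** (Allocation, Randomization, and blinding): patients are "randomly assigned to either the traditional vNOTES group or the gasless vNOTES group in a 1:1 ratio", by opaque envelope. The section says nothing about strata in either direction. The physician confirms the primary disease before the envelope is opened.
- **Baseline data** (Data collection): "Age, BMI, ASA status, clinical diagnosis, history of spontaneous delivery, abdominal surgery history, and surgical index", and MAP and HR before induction (T0).
- **Outcome** (Outcome measures): "The primary outcome is vital signs at the different time points", T0 to T7. Duration of surgery and anaesthesia, sufentanil and cisatracurium consumption, and blood loss are secondary.
- **Analysis** (Statistical methods): primary outcome data are "presented as mean ± standard deviation if normally distributed, and t-test will be conducted", with nonparametric tests otherwise. No covariate is named. That sentence is worded for the primary outcome. No other method is given for continuous secondary outcomes, so I take the same tests to be meant for them.

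**The concern.** A two-group t-test carries all between-patient variation in its standard error, including the part that baseline data could explain. Two such sources are already on the case report form: the patient's own T0 value, for MAP and HR, and the diagnosis, which separates uterine from adnexal operations.

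The Discussion frames the trial as a trade-off. Gasless surgery may spare haemodynamic disturbance, while CO2 may shorten surgery and reduce complications. Duration and blood loss are therefore part of the judgement, and they are outcomes that could plausibly depend on the kind of operation. If one arm happened to receive more adnexal cases, an unadjusted comparison could hide or mimic a difference in duration, and the reader would have no adjusted estimate to check it against.

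**Working it through.** No figure in the article rests on this point, so there is no stated value to reproduce. The 80% power used in step 3 is the article's nominal target and serves only as a reference level. The stated 49 per arm does not follow from the stated 10% reduction (50% versus 40%, one-sided 0.05, 80% power needs 305 per arm), which is a separate matter.

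**Inputs from the article:** 120 patients, 60 per arm, 1:1; one-sided α of 0.05 and 80% power (Sample size estimation). **Assumptions:** share of one diagnosis class 50% or 30%; allocation not stratified by diagnosis; R² of the baseline covariates 0.02 to 0.30. The article gives none of these.

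**1. Chance of case-mix imbalance.** With K of the 120 patients in a class, the number X falling in one arm of 60 is hypergeometric. The difference in proportions is |2X − K|/60.

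| Difference of at least | 50/50 mix (K = 60) | 30/70 mix (K = 36) |
|---|---|---|
| 10 points | 36.1% | 31.9% |
| 15 points | 10.0% | 7.2% |
| 20 points | 4.4% | 2.8% |

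The standard deviation of the difference is 0.092 and 0.084 respectively.

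**2. What an imbalance does to an estimate.** In a 50/50 mix where diagnosis explains R² of the variance, the two classes differ by 2√R² standard deviations. An imbalance of 10 points shifts the arm difference by 0.10 × 2√R². The unadjusted standard error is √(2/60) = 0.183 SD.
- R² 0.10: 0.10 × 0.632 = 0.063 SD, or 0.063/0.183 = 0.35 standard errors.
- R² 0.30: 0.10 × 1.095 = 0.110 SD, or 0.110/0.183 = 0.60 standard errors.

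**3. Gain in precision.** Adjustment multiplies the variance of the mean difference by 1 − R². For a comparison with 80% power unadjusted, adjusted power is Φ[(1.645 + 0.842)/√(1 − R²) − 1.645]. The matching sample size in place of 49 is 49 × (1 − R²), rounded up.

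| R² | Adjusted power | Equivalent n per arm |
|---|---|---|
| 0.02 | 80.7% | 49 |
| 0.05 | 81.8% | 47 |
| 0.10 | 83.5% | 45 |
| 0.20 | 87.2% | 40 |
| 0.30 | 90.8% | 35 |

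For MAP and HR, R² is the share explained jointly by T0 and diagnosis class. For the secondary outcomes it is the share explained by diagnosis class alone.

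**4. Validity of the unadjusted test.** In 200,000 simulated trials per setting, with 60 per arm, a 50/50 class and no treatment effect, the t-test rejected at the 5% level in 4.9%, 5.0% and 5.0% of trials at R² of 0, 0.1 and 0.3.

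**5. Cost if the covariates are useless.** Arm, two diagnosis indicators and T0 leave 120 − 5 = 115 residual degrees of freedom, against 120 − 2 = 118 for the t-test.

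**The case against.** The best defence is that nothing here is an error. Randomisation already allows for chance imbalance, step 4 confirms nominal type I error, and the article is condensed, so covariates may stand in a plan that is not shown. The validity part stands in full. The last part stands only partly: the article does not just leave the analysis open, it names the tests.

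It is also fair that relevance to the sizing endpoint is not shown. Sizing uses blood pressure at the start of surgery, T0 to T2 precede surgery, and one incision is described for every patient. Case mix probably explains little at T3 and more at T5 to T6, for duration and for blood loss. This limits the diagnosis covariate but not T0. The Background speaks of changes in MAP and HR, so T0 might be thought already used through change scores. With correlation ρ, a change score has variance proportional to 2(1 − ρ) and the adjusted model 1 − ρ². The first exceeds the second by (1 − ρ)², so adjustment is never less precise beyond the degree of freedom spent.

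A reader might infer more than the documents support:
- **That randomisation is unstratified.** The article is silent on this. If diagnosis is in fact a stratum, step 1 falls away, but a model containing it is then still the natural analysis.
- **That the χ2 and Fisher tests are also at fault.** At 49 per arm and 50% versus 25.9% (the rates that 49 would fit), χ2 versus Cochran-Mantel-Haenszel power is 80.5% versus 79.7% when control rates do not differ by procedure, and 80.8% versus 81.3% at 60%/40%. Only at 70%/30% does a gain appear (80.3% versus 84.6%). The documents do not support that assumption.
- **That planned procedure is available as a covariate.** It is not a listed variable, and diagnosis does not settle it: fibroids may lead to myomectomy or hysterectomy.

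**Conclusion.** The point holds as one of efficiency and interpretation. The stated tests are valid, but they leave T0 and diagnosis unused, although both are collected.

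A case-mix difference of 10 points or more has about a one-in-three chance, and of 15 points or more between 7% and 10%. These figures assume 60 analysed per arm, no stratification by diagnosis, and a 30/70 or 50/50 mix. It would be wrong to call such an imbalance the expected outcome, or to call the unadjusted estimate biased.

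The gain from adjustment is under 2 power points at R² up to 0.05 and about 11 at R² 0.30. A reader might go further and equate adjustment with 25% to 67% more patients. That needs R² of 0.2 to 0.4, from 1/(1 − 0.2) = 1.25 and 1/(1 − 0.4) = 1.67, and the article gives no basis for those values, least of all for blood pressure at T3. The recommendation does not depend on a large R², since adjustment costs almost nothing if R² is small. If an unshown plan already specifies such a model, the article's Statistical methods only need to be brought into line with it.

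**What to change.** Leave randomisation as it is. Before anyone sees data by group, replace the unadjusted comparisons of continuous outcomes with:

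- **MAP and HR:** at each analysed time point after T0, a linear model with arm, diagnosis class (uterine, adnexal, other) and the T0 value.
- **Duration of surgery and anaesthesia, anaesthetic consumption, blood loss:** a linear model with arm and diagnosis class, on a transformed scale where the data are skewed.
- **Sensitivity:** the t or nonparametric tests as now stated.

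Diagnosis class should be coded from the diagnosis recorded before the envelope is opened, not from the operation performed, which can be affected by allocation. The coding rule, including patients with both uterine and adnexal disease, should be written down in advance. The χ2 and Fisher comparisons can stay.

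The cost is a few sentences of analysis wording, the coding rule and three degrees of freedom at most. No new data are needed, and recruitment and allocation are unaffected.
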